### Background

After introduction of the pneumococcal conjugate vaccine (PCV), invasive pneumococcal disease (IPD) and subsequent pneumococcal mortality has been reduced globally. Yet in 2015, pneumococcal infections are still estimated to cause 294,000 (range 192 –366,000) deaths in HIV-uninfected children under 5 years.(1) Some populations are at higher risk for IPD including young infants and specific ethnicities such as Aboriginal, Māori or Pacific people.(2, 3)

Several PCVs are commercially available and cover different serotypes (7-valent PCV (PCV7);10-valent PCV (PCV10) (Synflorix, GSK); 13-valent PCV (PCV13) (Prevenar 13, Pfizer)). In comparison with PCV10, PCV13 also includes the serotypes 3, 6A, and 19A. Previous studies comparing the impact of PCV10 and PCV13 programmes until 2017 have not found superiority for one of the two vaccines in the overall burden of pneumococcal disease.(4-6) The World Health Organization recommends that a switch in PCV programme should be made when epidemiology of IPD changes considerably.(6)

In the national immunisation programme of Australia PCV13 is used since 2011, whereas Aotearoa New Zealand (NZ) switched from PCV13 to PCV10 in 2017 (Appendix 1).(7, 8) When NZ switched to PCV10 in 2017 it was on the basis that immunogenicity studies suggested the inclusion of serotype 19F in PCV10 offers cross-protection for serotype 19A. Whether this cross-protection is sufficient to protect for infection by serotype 19A has been questioned.(9, 10) A recent NZ study showed that serotype 19A in IPD patients increased from 12% in 2017 to 21% in 2020 with overall IPD incidence remaining similar. Furthermore, half of the hospital admissions in children <5 years with IPD was due to serotype 19A, and penicillin-resistance in serotype 19A increased to 60%.(10) Recently, this trend of increasing serotype 19A infections has been noticed in several other countries around the world who use PCV10 on their infant immunisation schedule.(11-15)

Australia and New Zealand have had similar experiences in the COVID-19 pandemic with relatively low case numbers compared to other countries. As containment measures in the COVID-19 pandemic have shown to reduce IPD (16), Australia and New Zealand are relatively comparable in their IPD incidence. To our knowledge, no previous study has examined the influence of different

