### Study objective

To compare IPD incidence and epidemiology between Australia and New Zealand in 2017-2021, with a focus on ethnicity, age and serotype 19A.

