### Methods

**Study design:** This is an ecological study based on surveillance data from Australia and NZ

**Data collection:** We will collect IPD case notification data from national surveillance institutes (National Notifiable Diseases Surveillance System (NNDSS), EpiSurv) and merge those with census data that will be derived from Australian Bureau of Statistics and Statistics New Zealand. In NZ, all laboratories contribute to the surveillance system.

IPD is defined as a laboratory confirmed infections of *S. pneumoniae* if isolated from a normally sterile site or detected with nucleic acid testing from a sterile site. To be able to compare cases between Australia and NZ, cases detected from a newer generation *S. pneumoniae* antigen test on cerebrospinal fluid or pleural fluid will be excluded (NZ only). (17, 18)

National coverage of childhood immunisation data will be extracted from the National Immunisation registers in NZ and Australia. Fully immunised was defined as eligible children who have completed all of their age-appropriate immunisations by the time they turned the milestone age.

**Sample size:** This is a descriptive study so a power calculation is not required. Preliminary data show us that in 2019 overall IPD rates per 100,000 for Australia and New Zealand are on average 8.4 (95%CI 8.1-8.8), and 9.9 (95%CI 9.1-10.8), respectively. Therefore, this study will provide estimates for IPD rates with sufficient certainty.

**Data analysis:** First, we will compare overall IPD rates per 100,000 and the proportion of cases with serotype 19A between Australia and New Zealand between 2017-2021. Second, we will perform a stratified analysis for ethnicity: Indigenous (Aboriginal and Torres strait islander) versus non-Indigenous for Australia, and Māori and Pacific vs other for New Zealand. Next, we will analyse of IPD rates and serotype 19A rates in different age groups. Furthermore, we will explore whether differences in IPD rates can be explained by differences in national immunisation coverage for pneumococcal vaccinations. In a sensitivity analysis, we will repeat all the analyses only including non-Indigenous children in Australia because Indigenous children receive additional doses of PCV in certain regions (Appendix 1). Cases with missing indigenous status were counted as non-indigenous.

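### The overall serotype 19A comparison between countries is set as a share of cases, which does not track 19A incidence when total IPD differs between countries or years

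*Protocol*

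**What the plan says.** The Study objective is to compare IPD incidence and epidemiology between the two countries in 2017-2021, "with a focus on ethnicity, age and serotype 19A". The Impact section promises insight into serotype rates and a comparison of the PCV10 and PCV13 programmes.

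In Methods, Data analysis, the opening step compares total IPD as a rate per 100,000 and, beside it, "the proportion of cases with serotype 19A between Australia and New Zealand between 2017-2021". The ethnicity step that follows names no measure. The age step is the only place where a 19A rate appears: "we will analyse of IPD rates and serotype 19A rates in different age groups". The text does not say whether the denominator of the proportion is all cases or serotyped cases. The case definition admits cases "detected with nucleic acid testing from a sterile site".

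The Sample size paragraph gives the 2019 total rates for Australia and New Zealand as "on average 8.4 (95%CI 8.1-8.8), and 9.9 (95%CI 9.1-10.8), respectively". The Background reports that the 19A share in New Zealand "increased from 12% in 2017 to 21% in 2020 with overall IPD incidence remaining similar", and also that "containment measures in the COVID-19 pandemic have shown to reduce IPD".

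**The concern.** A share and a rate answer different questions. The share says how much of a country's IPD is 19A; the rate says how much 19A disease there is per head. The stated aim is incidence, and the contrast of interest is between a programme whose vaccine contains 19A and one whose vaccine does not. Only the rate answers that directly.

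The share equals the rate only up to division by total IPD, and the protocol's own figures show that total IPD differs between the two countries. It may also change within the study window, because 2020 and 2021 are included. The all-age serotype result could then show a difference where 19A incidence is equal, no difference where it is unequal, or, for modest differences, the wrong country as higher. That matters because the protocol intends its results to inform national vaccine decisions.

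**Working it through.** **Inputs.** Total IPD rates for 2019, 8.4 and 9.9 per 100,000 (Methods, Sample size). New Zealand 19A share, 12% in 2017 and 21% in 2020 (Background). The 19A rates, the fall in other serotypes and the typed shares used below are assumptions; the protocol gives none of them.

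**The protocol's own figures.** Counts and populations are not given, so the rates cannot be rebuilt, only checked for coherence. From the interval width on the log scale, events ≈ [2 × 1.96 / ln(upper/lower)]²:
- Australia: [3.92 / ln(8.8/8.1)]² ≈ 2,237 events, implying about 26.6 million people at 8.4 per 100,000.
- New Zealand: [3.92 / ln(10.8/9.1)]² ≈ 524 events, implying about 5.3 million people at 9.9 per 100,000.

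Exact Poisson limits reproduce both intervals for counts in these ranges, so the stated rates are coherent and can be used.

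**Identity.** With every case typed, share = 19A rate / total IPD rate. Hence the share ratio (New Zealand/Australia) = 19A rate ratio ÷ (9.9/8.4) = 19A rate ratio ÷ 1.18.

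**Between countries, 2019 totals.**
- Equal 19A rate of 1.2 (assumed): 1.2/8.4 = 14.3% in Australia; 1.2/9.9 = 12.1% in New Zealand.
- Equal share of 12%: 0.12 × 8.4 = 1.01 against 0.12 × 9.9 = 1.19 per 100,000. Equal share of 21%: 1.76 against 2.08. Both are rate ratios of 1.18 that the share does not show.
- Reversal: a rate ratio between 1.00 and 1.18 gives a share ratio below 1. For example, 1.3 in New Zealand against 1.2 in Australia (assumed) gives 1.3/9.9 = 13.1% against 14.3%.
- Above 1.18 the direction is right but the contrast shrinks. An assumed rate ratio of 1.75 would appear as 1.75/1.18 = 1.48.

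**Over time.** Start at New Zealand's 9.9 with 12% 19A: 19A = 1.188, other serotypes = 8.712.
- Others fall by 30% (assumed) and 19A is unchanged: 1.188 / (1.188 + 0.70 × 8.712) = 1.188/7.286 = 16.3%.
- The same sum for assumed falls of 20%, 40% and 50% gives 14.6%, 18.5% and 21.4%. A fall of about 49% in the others would produce 21% with no rise in 19A.
- If all serotypes, 19A included, fall by 30%, the share stays at 12% while the 19A rate drops from 1.19 to 0.83.

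**Untyped cases.** If they stay in the denominator, observed share = true share × fraction typed. A true 12% reads as 11.4%, 10.8%, 9.6% or 8.4% when 95%, 90%, 80% or 70% of cases are typed (assumed range). A crude 19A rate is diluted by the same factor: a true 1.2 with 80% typed is counted as 0.96.

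**The case against.** The strongest reply has four parts.

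- **A proportion is a legitimate descriptive measure.** The objective covers epidemiology as well as incidence, and a share has one real advantage: if a country ascertains all serotypes equally well or badly, that factor cancels. This stands, and is a reason to keep the share as a secondary measure.
- **19A rates are already planned by age, and the total rate sits beside the share.** A reader might infer that no 19A rate is planned at all; that would be wrong. If the denominator is all cases, share × total rate recovers the overall rate of identified 19A. This lowers the stakes. It still leaves the reader to derive the result that the objective asks for, and it depends on a denominator that the text does not name.
- **The New Zealand signal in the Background is not an artefact of the measure.** With total incidence similar, 12% to 21% is a rate ratio of about 0.21/0.12 = 1.75, so there the share did follow the rate. This stands for that series. It rests on a stable total, which cannot be assumed through 2021 or between countries.
- **Serotypes 3 and 6A are outside the declared focus.** The Background notes "In comparison with PCV10, PCV13 also includes the serotypes 3, 6A, and 19A", and a reader might infer that leaving out 3 and 6A is an error. The objective singles out 19A and the Background explains why, so nothing in the objective is contradicted. Their absence only narrows the programme comparison claimed under Impact.

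A reader might also infer that untyped cases are to be counted as not 19A. The text does not say so, gives no typed share, and does not say that typing differs between countries. Such handling may belong to an analysis plan that is not shown.

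**Conclusion.** The point holds in a limited form: the protocol fixes the all-age 19A comparison as a proportion although its aim is incidence, and a better measure is available from counts and populations the study already needs. This is a choice the protocol makes, not a detail left for later.

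The distortion between countries is a factor of 1.18 at the 2019 totals. It lowers New Zealand's share relative to its rate, and reverses the direction only for rate ratios between 1.00 and 1.18. The factor comes from one year and will differ in others. It would be too strong to say that the serotype result will point the wrong way: a large difference in 19A incidence would still show in the right direction, though reduced.

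The 16.3% example assumes that other serotypes fall by 30% while 19A does not. The protocol gives neither the size of the pandemic fall nor its split by serotype. The effect of untyped cases cannot be sized from the protocol at all.

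**What to change.** - In Data analysis, make 19A incidence per 100,000 by country and year, with confidence intervals, the main serotype comparison: overall and by ethnicity as well as by age.
- Keep the proportion as a secondary measure. Name serotyped cases as its denominator and report the percentage typed by country and year.
- As a sensitivity analysis, scale the 19A rate up for untyped cases. The downside is that this assumes untyped cases resemble typed ones.
- Optionally, add rates for serotypes 3 and 6A and for types in neither vaccine. These would serve the programme comparison under Impact. Types in neither vaccine are an imperfect check on surveillance differences, because serotype replacement may move them too.

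The first two changes cost a few table rows. They need 19A, other-type and untyped counts by country and year, and by age and ethnicity for the stratified rates. The protocol does not list the variables requested, and Ethical considerations describes the surveillance data as aggregated, so this breakdown should be written into the data request. The optional items depend on whether the aggregated data carry that serotype detail. Some 19A cells by ethnicity and year may be small and their intervals wide.

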## Appendix 1 – Important changes in immunisation schedules for children in Australia and New Zealand over time

### Australia (7, 20)

|          |                                                                                         |                                                                                                                                                                                             |
|----------|-----------------------------------------------------------------------------------------|---------------------------------------------------------------------------------------------------------------------------------------------------------------------------------------------|
| 2001-Jun | Introduction PCV7 in Indigenous children and children with high-risk medical conditions | Indigenous : PCV 7 at 2, 4 and 6 months (PCV7), in high-incidence jurisdictions* PPV23 at 18-24 months, Medically high-risk : PCV7 at 2, 4, 6 and 12 months, PPV23 at 5 years |
| 2005-Jan | Universal 3 dose program PCV7                                                           | 2, 4 and 6 months (PCV7), with catch-up doses in children <2 years                                                                                                                          |
| 2011-Jul | PCV13 replaced PCV7                                                                     | Catch-up dose of PCV13 for children 12-35 months. Indigenous : in high-incidence jurisdictions PCV13 replaced PPV23 at 18-24 months.                                                 |
| 2018-Jul | PCV13 at different timings, change to 2+1                                               | PCV13 at 2, 4 and 12 months. Indigenous children in high-incidence jurisdictions*, and children at medically higher-risk : PCV 13 at 2, 4, 6 and 12 months (3+1)                     |

\*High-incidence jurisdictions: Northern Territory (NT), South Australia (SA), Queensland (QLD) and Western Australia (WA).

Indigenous: includes Aboriginal and Torres Strait Islander

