### New Zealand (8)

|          |                                                                                                               |                                                                                                                                   |
|----------|---------------------------------------------------------------------------------------------------------------|-----------------------------------------------------------------------------------------------------------------------------------|
| 2006     | PCV7 for high-risk children                                                                                   |                                                                                                                                   |
| 2008-Jun | Universal PCV7                                                                                                | PCV7 at 6 weeks, 3, 5 months and 15 months                                                                                        |
| 2011     | PCV10 replaced PCV7                                                                                           | For high-risk children : PCV13 replaced PCV7                                                                               |
| 2014     | PCV13 replaced PCV10                                                                                          |                                                                                                                                   |
| 2015     | PCV13 available for patients of any age with certain high-risk conditions                                     |                                                                                                                                   |
| 2017     | PCV10 replaced PCV13                                                                                          | PCV13 continues for high-risk individuals                                                                                         |
| 2020     | PCV10 dosing change: 2-dose primary schedule plus booster dose given at 6 weeks, 5 months and 12 months (2+1) | For high-risk infants : PCV13 remained at 3-dose schedule plus booster for high-risk infants (6 weeks, 3, 5 and 12 months) |

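### Milestone-age 'fully immunised' stands for different PCV courses in Australia and New Zealand and changes meaning within 2017-2021, so it is not a like-for-like measure of pneumococcal coverage

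*Protocol*

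**What the plan says.** The Protocol, Methods, describes the design in these words: "This is an ecological study based on surveillance data from Australia and NZ". On coverage it states: "National coverage of childhood immunisation data will be extracted from the National Immunisation registers in NZ and Australia". The one coverage measure defined is this: "Fully immunised was defined as eligible children who have completed all of their age-appropriate immunisations by the time they turned the milestone age". No milestone age is named, and the measure refers to all immunisations, not to PCV. Under Data analysis, after the age-group comparison, the plan adds that "we will explore whether differences in IPD rates can be explained by differences in national immunisation coverage for pneumococcal vaccinations".

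Appendix 1 gives the schedules. The universal Australian programme of 2005 is listed as "2, 4 and 6 months (PCV7), with catch-up doses in children <2 years". The 2011 switch to PCV13 lists no new universal timing. From July 2018 the doses fall at 2, 4 and 12 months. For New Zealand the 2008 entry is "PCV7 at 6 weeks, 3, 5 months and 15 months". No new timing is listed until 2020, when doses move to 6 weeks, 5 months and 12 months. The Impact section expects the results to compare the PCV10 and PCV13 programmes and to inform decisions on them.

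**The concern.** A coverage figure can only be weighed as a rival explanation for a rate difference if it counts the same thing on both sides. Here the measure is tied to whatever each country's schedule requires at the milestone. The required PCV course differs between the countries and changes once in each of them inside the study window.

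This could mislead in two ways. Similar percentages could be taken to mean similar PCV exposure when the courses behind them differ. A lower percentage in New Zealand could be taken as under-vaccination when it reflects only a later dose that Australia's schedule did not require. Year-to-year movement in either country could also come from the schedule change and not from uptake. Because the study is meant to bear on the choice between vaccines, a misread coverage comparison feeds directly into that question.

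**Working it through.** **The plan's own figures.** The protocol gives no coverage figure. Its only planning numbers are the 2019 rates per 100,000 for Australia and New Zealand, which "are on average 8.4 (95%CI 8.1-8.8), and 9.9 (95%CI 9.1-10.8), respectively". Without case counts these cannot be rebuilt exactly, but they are plausible Poisson intervals. With SE = CI width / (2 × 1.96), cases ≈ (rate / SE)². This gives about 2,213 cases for Australia and 521 for New Zealand, with implied populations of 26.3 and 5.3 million. The gap to be explained is 9.9 / 8.4 = 1.18 (about 1.07 to 1.30). No stated figure is shown to be wrong.

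**Step 1: PCV doses required of a complete child (universal schedule, Appendix 1).** The PCV7-era timings are carried forward until the next listed timing change.

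| Schedules in force | Australia | New Zealand | Due before 12 months | Due by 24 months |
|---|---|---|---|---|
| Jan 2017 to Jun 2018 | 2, 4, 6 months | 6 weeks, 3, 5, 15 months | 3 v 3 | 3, no booster v 4 with booster |
| Jul 2018 to the 2020 change | 2, 4, 12 months | 6 weeks, 3, 5, 15 months | 2 v 3 | 3 with booster v 4 with booster |
| After the 2020 change | 2, 4, 12 months | 6 weeks, 5, 12 months | 2 v 2 | 3 with booster v 3 with booster |

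The entry changes down each column and differs across countries in two of the three periods at 24 months. Appendix 1 also lists additional doses for Indigenous children in certain jurisdictions and for high-risk children, so one national percentage mixes courses within a country as well.

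**Step 2: how long this lasts at a 24-month milestone (assumed; the protocol names none).** Children reaching 24 months in January 2017 to December 2021 were born in January 2015 to December 2019.

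- Australian children already past 12 months in July 2018 were born before July 2017 and reach 24 months before July 2019. Appendix 1 lists no catch-up for the 2018 change, so the no-booster course applies to January 2017 to June 2019, which is 30 of 60 months.
- If New Zealand's change came as early as January 2020, children past 15 months by then were born before October 2018 and reach 24 months before October 2020. The 3+1 course therefore faces all 30 of those months.
- The new New Zealand course applies from the start only to children under 3 months old at the change. They were born from October 2019 at the earliest and reach 24 months from October 2021. Fully matched 2+1 courses thus occupy at most 3 of 60 months. Cohorts in between are transitional.

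**Step 3: direction of a possible misreading.** Assume 95% complete three doses in each country on the older schedules, that PCV alone decides completeness, and that New Zealand booster uptake among those children is 80% to 100%.

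- Reported at 24 months: Australia 95%; New Zealand 0.95 × 0.80 = 76% to 0.95 × 1.00 = 95%. At 90% uptake it is 0.95 × 0.90 = 85.5%.
- Doses per child from those courses: Australia 0.95 × 3 = 2.85; New Zealand 2.85 + 0.76 = 3.61 to 2.85 + 0.95 = 3.80. At 90% uptake it is 2.85 + 0.855 = 3.705.

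New Zealand would look equally or less well covered although its children had received more doses. This is a count of exposure and says nothing about which schedule protects better.

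**Step 4: what two national series can separate.** With one rate and one coverage value per country, a design with intercept, country and coverage has rank 2 of 3. With 2 × 5 = 10 country-years, year effects and coverage constant within country, the rank is 6 of 7. If coverage varies by year (assumed 3-point country gap, 0.5-point yearly SD), the rank is 7 of 7. That leaves 3 residual degrees of freedom, and the variance inflation from the country-coverage correlation is about 13.

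**The case against.** The strongest reply is that the protocol declares a descriptive, ecological study and says only that it will explore coverage. No model, test or decision rule is attached. Confounding of country with vaccine product is inherent in any two-country comparison. That stands, so Step 4 is a reason to limit the wording of the conclusion and not a defect in itself.

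Several stronger readings are tempting, but the document does not support them.

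- A reader might infer that coverage and IPD cases are mismatched by birth cohort. The protocol is silent on alignment, age-group rates are planned, and an analysis plan that is not at hand could set the link.
- A reader might infer that percentages at 12 months conceal a large gap on the older schedules, because Australia's course had ended and New Zealand's had not. A complete child in either country had had three doses by then. The difference concerns the later booster.
- A reader might infer that the analysis can show nothing. Comparable dose-specific coverage, or higher coverage in the country with the higher rate, would be weak descriptive evidence against coverage as the explanation. The serotype 19A comparison also bears on product versus uptake.

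It can also be said that the schedule without a booster was in force for only 18 of 60 study months, that the dose timings come from PCV7-era rows, and that a missed New Zealand booster would show in the reported percentage. The first is true by calendar, but at a 24-month milestone the contrast lasts longer (Step 2). The second is a fair caution about an inference that Appendix 1 makes reasonable. On the third, the gap would be visible but could point the wrong way (Step 3).

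**Conclusion.** The point holds for the measure. The coverage rule in Methods, read with Appendix 1, compares unlike PCV courses and changes meaning within each country during the window. At 24 months on the older schedules the contrast is three doses without a booster against four with one. It then becomes three against four, both with a booster, and matches for at most the last 3 of 60 months.

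This rests on Appendix 1 listing every universal timing change, on a 24-month milestone, and on no catch-up at the 2018 change. A milestone before 12 months would show a smaller and different contrast: 3 v 3, then 2 v 3, then 2 v 2. The percentages in Step 3 are assumptions and only illustrate direction. The rate comparisons themselves are unaffected. The matter deserves correction before the register extract is specified, because the results are intended to inform vaccine policy.

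**What to change.** In Methods, Data collection, replace the all-immunisation measure with PCV-specific coverage by dose. Report primary series and booster separately, at the same named ages in both countries, including one age after the last booster, such as 24 months. State for each year which schedule applied.

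In Data analysis, set these figures descriptively beside under-5 IPD rates by age group and year, and keep cases under 24 months. Restricting the link to 24-59 months would drop the young infants whom the Background names as high risk. It would also leave only the 2015-2016 births fully observed, largely before New Zealand's move to PCV10. Reword the aim from explaining the difference to describing coverage alongside it. Add that two national series cannot separate coverage from vaccine product and schedule.

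The cost is a short text change, a more detailed extract from the same registers (assuming they can supply counts by dose, which the protocol does not state), and a weaker conclusion.

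### The coverage exploration uses all-serotype IPD as its only outcome, so a product-related difference in serotypes 3, 6A and 19A is mixed into what coverage is asked to explain; add a shared-serotype outcome

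*Protocol*

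**What the plan says.** The coverage step is a single sentence in Methods, Data analysis: "we will explore whether differences in IPD rates can be explained by differences in national immunisation coverage for pneumococcal vaccinations". The case definition under Data collection covers any laboratory-confirmed pneumococcal infection "isolated from a normally sterile site or detected with nucleic acid testing from a sterile site"; serotype plays no part in it. The sentence just before the coverage step treats total and 19A disease as two outcomes: "we will analyse of IPD rates and serotype 19A rates in different age groups". All-serotype IPD is therefore the natural reading of the outcome for coverage. The protocol nowhere names an outcome limited to vaccine serotypes, or to serotypes that the two vaccines share.

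On the products, the Background states: "In comparison with PCV10, PCV13 also includes the serotypes 3, 6A, and 19A". It also says that Australia has used PCV13 since 2011 and that New Zealand changed from PCV13 to PCV10 in 2017. Appendix 1 agrees, and shows New Zealand on PCV13 from 2014 until that change, with PCV13 kept for high-risk individuals afterwards.

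**The concern.** The Impact section presents the study as a real-life comparison of PCV10 and PCV13 programmes that will inform vaccine decisions. A difference in coverage is an obvious rival explanation for a country difference, so the coverage step should help the reader weigh it. All-serotype IPD suits that purpose poorly, for two reasons.

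- **Confounding.** Product is largely aligned with country, and coverage is a national figure. If New Zealand had lower coverage and also more 3/6A/19A disease because of PCV10, total IPD would be higher there, and the analysis could not show which of the two was responsible.
- **Attenuation.** Serotypes in neither vaccine add cases that are not expected to respond directly to coverage. They pull a relative effect towards 1.

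The ten serotypes in both vaccines should respond to coverage with much less interference from the choice of product. The plan does not use them.

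**Working it through.** **1. The protocol's own rates.** Rates per 100,000 in 2019 for Australia and New Zealand "are on average 8.4 (95%CI 8.1-8.8), and 9.9 (95%CI 9.1-10.8), respectively". The gap is 9.9 - 8.4 = 1.5 per 100,000, a rate ratio of 9.9/8.4 = 1.18 (95% CI about 1.07-1.30, from the stated intervals). With events = 1/[ln(upper/lower)/3.92]², the intervals imply:
- Australia: ln(8.8/8.1)/3.92 = 0.0211, about 2,240 cases a year.
- New Zealand: ln(10.8/9.1)/3.92 = 0.0437, about 520 cases a year.

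The protocol gives no counts or denominators, so this is a consistency check and not a full reproduction.

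**2. How much of the gap could be 19A?** For New Zealand the Background reports that "serotype 19A in IPD patients increased from 12% in 2017 to 21% in 2020 with overall IPD incidence remaining similar". Applied to the 2019 rate, 12-21% of 9.9 is 1.19-2.08 per 100,000. No Australian 19A share is given. Assuming 2-12%, the Australian 19A rate is 0.17-1.01 per 100,000. Then:
- Smallest difference: 1.19 - 1.01 = 0.18, or 12% of the gap.
- Largest difference: 2.08 - 0.17 = 1.91, or 127% of the gap.

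So 19A alone might contribute little or more than the whole gap, and serotypes 3 and 6A come on top. In young children the share is probably larger: the Background reports for New Zealand that "half of the hospital admissions in children <5 years with IPD was due to serotype 19A".

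**3. Attenuation.** Let c be coverage, VE direct effectiveness and v the share of IPD from the ten shared serotypes. The protocol gives none of these, so all values here are assumptions, and the direction (New Zealand lower) is assumed too.

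RR(shared) = (1 - c_NZ × VE)/(1 - c_AU × VE); RR(all) = 1 + v × [RR(shared) - 1].

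With coverage of 95% (Australia) and 90% (New Zealand):
- VE 70%: 0.370/0.335 = 1.10.
- VE 90%: 0.190/0.145 = 1.31.

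| v | RR on all IPD in vaccinated ages |
|---|---|
| 10% | 1.01-1.03 |
| 30% | 1.03-1.09 |
| 50% | 1.05-1.16 |

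If all ages are pooled and 10% of cases fall in vaccinated ages (assumed, direct effect only), the range for v of 10-50% is 1.001-1.016. On the rate-difference scale there is no attenuation: the other serotypes add noise and confounding but leave the expected absolute difference unchanged.

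**4. Precision of a shared-serotype outcome.** Assume 10% of cases are under 5 years and 10-25% of those are shared serotypes. Over five years:
- New Zealand: 520 × 5 × 0.10 × (0.10 to 0.25) = 26 to 65 cases.
- Australia: 2,240 × 5 × 0.10 × (0.10 to 0.25) = 112 to 280 cases.

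The 95% CI factor is exp{1.96 × √(1/a + 1/b)}: 1.53 for 26 and 112 cases, and 1.31 for 65 and 280. Coverage of 94% v 91% with VE 80% would give an expected ratio of 0.272/0.248 = 1.10, well inside that margin.

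**The case against.** The step is labelled exploratory, in a study described as descriptive and ecological. No model or attribution rule is fixed. The same paragraph compares the 19A proportion between countries and reports 19A rates by age, so the main product-sensitive component will be visible beside the coverage result. An analysis plan that is not shown may group serotypes further. This limits the seriousness of the point. It does not remove it, because the outcome that the protocol names for this step fits the question badly.

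Product and country are also not perfectly aligned. New Zealand's earlier PCV13 use means that some of its young children early in the period were PCV13 cohorts. Nor is 19A wholly outside the reach of PCV10 coverage: the Background says the 2017 change relied on cross-protection from 19F and that its adequacy has been questioned. PCV13 coverage in Australia can affect 19A as well. The separation between the two serotype groups is useful but not clean.

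A reader might go further in four ways, none of which the documents support:
- **That a coverage effect is diluted almost to nothing.** This needs a small shared-serotype share or pooling of all ages, and applies only on the relative scale. At shares of 30-50% a clear part remains.
- **That the 19A rise is a known excess larger than any coverage signal.** The rise is 9.9 × (0.21 - 0.12) = 0.89 per 100,000, but this is a change over time within New Zealand, scaled to another year's rate, with total incidence reported as similar. It is not a country difference.
- **That the plan will credit product differences to coverage.** It leaves room for that reading but does not commit to it.
- **That a shared-serotype outcome would rule coverage in or out.** The precision above and the two-country design prevent this.

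**Conclusion.** The concern holds in a limited form. As written, the coverage exploration rests on all-serotype IPD. Product-related differences in 3, 6A and 19A are then mixed with any coverage effect, and non-vaccine serotypes attenuate that effect on the relative scale. The confounding follows from the protocol's own account of the products and their timing. Its size cannot be fixed: 12-127% of the 2019 gap for 19A alone depends on the assumed Australian share and on applying the 2017 and 2020 New Zealand shares to the 2019 rate. The attenuation likewise depends on assumed coverage, effectiveness and shared-serotype share. The change is worth making because it gives a more informative comparison at little cost; the rest of the study does not depend on it.

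**What to change.** Keep the all-IPD comparison. Add to the coverage analysis, in vaccine-eligible ages (for example under 5 years):
- IPD rates from the ten serotypes in both PCV10 and PCV13.
- IPD rates from 3, 6A and 19A, reported separately as the product-sensitive group.
- A New Zealand to Australia rate ratio with 95% CI for each group.

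State in advance that the reading is descriptive. A country difference confined to 3/6A/19A points away from coverage as the main explanation. A similar difference in the shared serotypes is compatible with coverage or with other country factors, such as the differing dose schedules in Appendix 1. Neither pattern should serve as a pass/fail rule, and a wide interval that includes 1 should not be read as showing no difference.

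The cost is protocol wording and a regrouping of serotype data, part of which the 19A analysis already needs. The drawbacks should be stated: few cases and wide intervals (a factor of about 1.3 to 1.5 either way under the assumptions above), reliance on cases that were serotyped, and an assumption that the two products act alike on the shared serotypes. With two countries, coverage still cannot be separated from other national differences.
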